## Abstract

**Background:**

Tripterygium glycoside tablets (TGTs), a traditional Chinese medicine–based therapy and a type of conventional synthetic disease-modifying antirheumatic drug (csDMARD), have shown promise as a cost-effective alternative for rheumatoid arthritis (RA). However, there is limited evidence regarding the most effective combinations with other csDMARDs, such as methotrexate, leflunomide, and hydroxychloroquine. This study evaluates the 12-week efficacy and safety of TGT-based regimens in patients with moderately active RA.

**Objective:**

This study aims to evaluate the clinical efficacy and safety of the csDMARD combination regimens mainly based on TGTs in the treatment of RA, using multicenter clinical data, and to explore the clinical characteristics of TGTs and identify the optimal combination therapy through a randomized controlled trial.

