## Introduction

Rheumatoid arthritis (RA) is a chronic autoimmune disease characterized by synovial inflammation and progressive joint destruction, leading to significant disability and reduced quality of life [1-3]. Globally, RA affects approximately 0.5% to 1% of the population [3-5], with a prevalence of 0.28% to 0.45% in China, affecting more than 5 million individuals [6,7]. The disease not only imposes a heavy burden on patients and their families but also places significant economic pressure on health care systems due to the need for long-term treatment and management of complications [7,8].

Despite significant progress in RA therapy, including the development of conventional synthetic disease-modifying antirheumatic drugs (csDMARDs), biologic disease-modifying antirheumatic drugs (bDMARDs), and targeted synthetic disease-modifying antirheumatic drugs (tsDMARDs), achieving remission remains a challenge [9-11]. Additionally, although bDMARDs and tsDMARDs are highly effective and can be used as monotherapy in certain cases, their cost-effectiveness compared with csDMARDs is still questionable. While bDMARDs and tsDMARDs have improved outcomes for many patients, their high cost and associated safety risks—such as increased susceptibility to infections, malignancies, and thromboembolic events—limit their accessibility, particularly in low- and middle-income countries [12-14].

In this context, Tripterygium glycoside tablets (TGTs), a traditional Chinese medicine–based therapy and a type of csDMARD, have emerged as a promising alternative [15]. TGTs have shown comparable efficacy to methotrexate in monotherapy and potential synergistic effects when combined with other csDMARDs [15-19]. However, robust evidence on the optimal combination strategy, safety profile, and efficacy of TGTs in patients with moderate disease activity remains scarce [17]. This subgroup of patients is often underrepresented in clinical trials but represents a significant proportion of real-world RA cases.

This trial aims to address these critical gaps by evaluating the 12-week efficacy and safety of TGTs combined with methotrexate, leflunomide, or hydroxychloroquine in a well-diagnosed population with RA. By focusing on short-term outcomes, the study seeks to identify the most effective and safest TGTs-based regimen, providing evidence to guide clinical practice and improve treatment outcomes for patients with RA globally.

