### Sample Size

The sample size was calculated for a multicenter RCT with 1 common control group (TGT monotherapy) and 3 active treatment groups (TGTs+methotrexate, TGTs+hydroxychloroquine, and TGTs+leflunomide). The primary hypothesis is that each combination therapy will be superior to TGTs monotherapy for the ACR20 response rate at week 12. The assumed ACR20 response rates were derived from an unpublished study conducted at our center in 2022 ([name], unpublished data, May 2022). This study included 30 patients with moderate RA (DAS28 3.2-5.1), randomized 1:1 to receive either TGT monotherapy (n=15) or TGTs+methotrexate (n=15) for 12 weeks. The observed ACR20 response rates were 53.3% (8/15) in the monotherapy group and 80% (12/15) in the combination group. On the basis of these data, the following assumptions were made:

TGT monotherapy—ACR20 response rate=54%

Combination therapy (TGTs+methotrexate, TGTs+hydroxychloroquine, and TGTs+leflunomide)—ACR20 response rate=80%

We consider this absolute difference of 26 percentage points to be clinically meaningful.

The sample size calculation was performed using PASS (Power Analysis and Sample Size) software (version 15; NCSS, LLC). The procedure selected was “chi-square tests” to compare multiple treatment groups with a common control while controlling the family-wise type I error rate.

Input parameters included the following: solving for sample size, degree of freedom 3; power 0.8; α=.05, and effect size (w=0.255098).

Consequently, the Dunnett procedure required 42 participants per group, resulting in a total sample size of 168 before accounting for dropouts. With an estimated dropout rate of 10%, the adjusted total sample size was approximately 188 participants, corresponding to approximately 47 participants per group.

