### Statistical Analysis

The primary outcome—the ACR20 response rate at week 12—will be compared between each combination therapy group and the TGT monotherapy group using logistic regression. The study center will be included as a fixed effect to account for potential site differences.

Secondary outcomes (eg, DAS28-ESR and CDAI) will be analyzed using mixed-effects models for repeated measures. These models will include fixed effects for treatment, visit, treatment-by-visit interaction, baseline value, and study center, with participants included as a random intercept.

All primary analyses will be conducted on the intention-to-treat population, defined as all randomized participants who received at least 1 dose of the study drug. Missing data will be handled using multiple imputation under the missing-at-random assumption, generating 20 imputed datasets. Sensitivity analyses will be performed to evaluate the robustness of conclusions under different missing data assumptions.

Safety data, including adverse events, will be summarized descriptively by treatment group. Between-group comparisons of adverse event rates will be conducted using the Fisher exact test.

Rescue therapy with NSAIDs was permitted for intolerable joint pain, in line with ethical requirements and standard clinical practice for the management of RA. As pain and swelling are universal symptoms of active RA, the requirement for rescue analgesia reflects real-world treatment conditions and will not be statistically adjusted in the primary analysis. The use of rescue medication will be documented descriptively and reported by treatment group. If notable between-group differences in the frequency of rescue therapy are observed, exploratory sensitivity analyses will be conducted to assess their potential influence on efficacy outcomes.

All analyses will be performed using SAS (version 9.4) and R (version 4.4.s2; R Foundation for Statistical Computing). Between-group differences will be reported with 95% CIs. Statistical significance is set at α=.05 (2-sided).

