## Discussion

### Summary of Anticipated Findings

This trial is expected to provide robust evidence on the comparative efficacy and safety of TGT-based combination therapies in patients with moderately active RA. We hypothesize that all 3 TGT combination regimens (TGTs+methotrexate, TGTs+hydroxychloroquine, and TGTs+leflunomide) will result in significantly higher ACR20 response rates at week 12 than TGT monotherapy. These findings are expected to clarify the risk-benefit profile of these combinations and identify which regimen offers the most favorable balance of efficacy and tolerability for different patient subgroups.

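### The aim is to identify the optimal TGT combination, but the primary hypothesis and analysis specify only contrasts with TGT monotherapy, and no contrast between combinations or selection rule is named

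*Protocol article*

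**What the plan says.** **Aim.** The Abstract (Objective) wants to "identify the optimal combination therapy through a randomized controlled trial". The Introduction says that "the study seeks to identify the most effective and safest TGTs-based regimen", and Study Design describes the trial as producing evidence on the optimal combination of TGTs with the three partner drugs. The Discussion (Summary of Anticipated Findings) expects to "identify which regimen offers the most favorable balance of efficacy and tolerability for different patient subgroups".

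**Hypothesis and primary analysis.** Sample Size states: "The primary hypothesis is that each combination therapy will be superior to TGTs monotherapy for the ACR20 response rate at week 12". Statistical Analysis follows this: week-12 ACR20 "will be compared between each combination therapy group and the TGT monotherapy group using logistic regression", with study center as a fixed effect.

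**Planning rates.** Sample Size assumes 54% ACR20 response on monotherapy and one common rate, 80%, for all three combinations.

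**Other analyses.** For the secondary outcomes: "These models will include fixed effects for treatment, visit, treatment-by-visit interaction, baseline value, and study center". For safety: "Between-group comparisons of adverse event rates will be conducted using the Fisher exact test". Between-group differences are to carry 95% CIs. None of these sentences says which pairs of groups are meant.

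**Status.** The Abstract (Results) reports 181 patients enrolled, data collection complete and statistical analyses not yet performed.

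**The concern.** Finding the best of three combinations is a question about differences among those three arms. Every efficacy contrast that the article names is against the fourth arm, and the planning rates set the differences among the three to zero. The article also gives no criterion for calling a regimen optimal.

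Whoever writes the results will therefore have three separate comparisons with monotherapy and a stated aim of naming a winner. If one combination reaches significance and another does not, or if one has the highest observed rate, it is easy to report it as the best regimen. Neither pattern is evidence that two combinations differ. At stake is the headline conclusion of the trial. The tests against monotherapy themselves remain interpretable.

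**Working it through.** **1. The plan's own figure.** Inputs from Sample Size: rates 0.54, 0.80, 0.80, 0.80; 3 degrees of freedom; power 0.80; α = 0.05; w = 0.255098.

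- Mean rate = (0.54 + 3 × 0.80)/4 = 0.735.
- w² = [(0.195² + 3 × 0.065²)/4] / (0.735 × 0.265) = 0.012675/0.194775 = 0.06508, so w = 0.2551, as stated.
- The noncentrality for 80% power is 10.9026, so N = 10.9026/0.06508 = 167.5, rounded up to 168, or 42 per arm, as stated.
- Dropout: 42/0.9 = 46.7, so 47 per arm and 188 in total, as stated.

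The whole effect size comes from the distance between monotherapy and the rest. Differences among the combinations contribute nothing to it.

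**2. How often do three equal combinations get different verdicts?** Assume the plan's rates are true, with two-sided pooled z tests and no center term. Given the monotherapy count x, the three tests are independent, each significant in favor of the combination with the same probability q(x). Then P(all) = E[q³], P(none) = E[(1 − q)³] and P(split) = 1 − P(all) − P(none). I computed these by exact binomial enumeration.

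Two inputs are uncertain, so I vary both. Arm size is 42 (planned evaluable) or 45 (181/4 = 45.25 enrolled). The critical value is 1.960, because Statistical Analysis states only a two-sided 0.05, or 2.349, the Dunnett value for three comparisons with a common control, because Sample Size names that procedure.

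| Per arm | Critical value | Power per comparison | All three | None | Split |
|---|---|---|---|---|---|
| 45 | 1.960 | 77% | 57.0% | 6.7% | 36.4% |
| 42 | 1.960 | 73% | 52.7% | 8.5% | 38.8% |
| 45 | 2.349 | 62% | 39.0% | 15.7% | 45.3% |
| 42 | 2.349 | 59% | 33.8% | 17.7% | 48.5% |

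So truly equal combinations receive mixed verdicts in about 36% to 48% of trials.

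**3. Are point estimates safer?** No. In 400,000 simulated trials with 45 per arm and all three combinations at 80%, one arm has the uniquely highest observed rate in about 84%. The best and worst observed rates differ by 10 points on average.

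**4. What could direct contrasts show at this size?** The article gives no expected difference between combinations, so the gaps below 80% used here are assumptions.

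- CI half-width for two arms at 80%: 1.96 × √(2 × 0.8 × 0.2/n) = 17.1 points at n = 42 and 16.5 at n = 45.
- Power for 80% versus 70% at unadjusted 0.05: about 18% to 20%.
- Gap below 80% detectable with 80% power at unadjusted 0.05: about 28 points at n = 42 and 27 at n = 45 by enumeration. The normal approximation gives 28.6 and 27.6.
- For 80% power at a 10-point gap, 294 per arm would be needed.

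Direct contrasts are therefore feasible as estimates with intervals, but not as a dependable way to select a winner.

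**The case against.** The primary hypothesis is explicit and coherent, and the primary analysis matches it. Exploratory pairwise contrasts are often left to a statistical analysis plan, which is not shown. All of that stands, and for that reason the absence of contrasts alone would not be a finding. What remains is that the article itself fixes the primary contrasts and they do not answer its own stated objective.

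Three stronger readings are tempting, and the text does not support them:

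- *A reader might infer that no analysis compares the combinations at all.* The repeated-measures models include treatment and treatment-by-visit terms, the Fisher tests are described only as between-group, and 95% CIs are promised for between-group differences. None of these is limited to monotherapy contrasts. A four-arm logistic model would also yield the combination contrasts. The accurate statement is that none is named.
- *A reader might infer that the arms will be ranked by their p-values against monotherapy.* The article gives no ranking rule of any kind. Ranking by estimates, or by efficacy and safety together, fits its wording equally well. The split in step 2 shows what such a reading would do; it does not describe a stated procedure.
- *A reader might infer that subgroup-specific selection is a study objective.* That phrase appears among the anticipated findings in the Discussion, not in the objective or in a planned analysis.

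It is also fair to object that requiring every pairwise interval to exclude zero before calling a regimen optimal would nearly guarantee that none is named at this sample size. That rule is debatable, and it is not proposed here.

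**Conclusion.** The mismatch holds in this form: the aim is to identify the optimal combination, while the specified hypothesis, primary analysis and sample size address only superiority over monotherapy. No efficacy contrast between combinations and no selection rule is specified. Following the plan as written cannot support a statement that one combination is better than another.

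The size depends on choices that the article leaves open. With truly equal combinations, mixed verdicts occur in about 36% of trials (45 per arm, unadjusted 0.05, power about 77% per comparison) to 48% (42 per arm, Dunnett, power about 59%). These figures rest on the plan's 54% and 80% rates and on tests without the center term or imputation. That monotherapy contrasts cannot rank the combinations does not depend on them.

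This should be corrected before analysis. It does not invalidate the comparisons with monotherapy.

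**What to change.** Before the analysis starts, in a dated amendment or in the statistical analysis plan:

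1. Pre-specify the three pairwise combination contrasts (methotrexate versus leflunomide, methotrexate versus hydroxychloroquine, leflunomide versus hydroxychloroquine) from the same four-arm, center-adjusted logistic model, and from the key secondary models. Report them as differences with 95% CIs that are either multiplicity-adjusted or labelled exploratory.
2. State that no combination will be called better than another on the basis of its result against monotherapy alone.
3. Reword the objective to superiority of each combination over monotherapy plus estimation of differences among combinations. Note the expected precision: half-width about 17 points, and 80% power only for gaps of about 27 to 28 points.
4. Label any subgroup-specific recommendation exploratory.

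The cost is three extra contrasts per model and some rewording; no new data are needed. The downside is a more modest headline objective and pairwise estimates that will be imprecise. Because recruitment is complete, the design cannot be changed to answer the selection question, but the contrasts and the interpretation can still be fixed in advance.

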**Methods:**

This multicenter, open-label randomized controlled trial recruited 188 participants (47 per group) from 3 hospitals. Eligible patients were stratified by study center and randomized in a 1:1:1:1 ratio to receive TGT monotherapy, TGT plus methotrexate, TGT plus leflunomide, or TGT plus hydroxychloroquine. The primary outcome was the American College of Rheumatology 20% improvement response rate. Secondary outcome measures included the Disease Activity Score-28 (DAS28) using erythrocyte sedimentation rate and DAS28 using C-reactive protein response rates, the Clinical Disease Activity Index, the Simplified Disease Activity Index, the pain visual analog scale (0 to 10 points), the patient global assessment, the medical doctor global assessment, quality of life (36-Item Short Form Health Survey), and the Health Assessment Questionnaire Disability Index. All enrolled patients were followed up every 4 weeks for a total of 12 weeks. Adverse events were recorded during the observation period of the study. All patients randomized in this study will be included in the intention-to-treat analysis.

**Results:**

This study was funded in February 2024. Funding was provided by the Beijing Tongzhou District Science and Technology Planning Project. Recruitment of participants commenced on September 1, 2024, and concluded on December 31, 2025. A total of 181 patients were enrolled. Final data collection has been completed, and data cleaning is currently underway. Statistical analyses have not yet been performed. The primary results are expected to be submitted for publication by the end of 2026.

**Conclusions:**

This trial uses multicenter clinical data to provide robust evidence on the efficacy and safety of TGTs in combination with csDMARDs for the treatment of RA with moderate disease activity.

## Introduction

Rheumatoid arthritis (RA) is a chronic autoimmune disease characterized by synovial inflammation and progressive joint destruction, leading to significant disability and reduced quality of life [1-3]. Globally, RA affects approximately 0.5% to 1% of the population [3-5], with a prevalence of 0.28% to 0.45% in China, affecting more than 5 million individuals [6,7]. The disease not only imposes a heavy burden on patients and their families but also places significant economic pressure on health care systems due to the need for long-term treatment and management of complications [7,8].

Despite significant progress in RA therapy, including the development of conventional synthetic disease-modifying antirheumatic drugs (csDMARDs), biologic disease-modifying antirheumatic drugs (bDMARDs), and targeted synthetic disease-modifying antirheumatic drugs (tsDMARDs), achieving remission remains a challenge [9-11]. Additionally, although bDMARDs and tsDMARDs are highly effective and can be used as monotherapy in certain cases, their cost-effectiveness compared with csDMARDs is still questionable. While bDMARDs and tsDMARDs have improved outcomes for many patients, their high cost and associated safety risks—such as increased susceptibility to infections, malignancies, and thromboembolic events—limit their accessibility, particularly in low- and middle-income countries [12-14].

In this context, Tripterygium glycoside tablets (TGTs), a traditional Chinese medicine–based therapy and a type of csDMARD, have emerged as a promising alternative [15]. TGTs have shown comparable efficacy to methotrexate in monotherapy and potential synergistic effects when combined with other csDMARDs [15-19]. However, robust evidence on the optimal combination strategy, safety profile, and efficacy of TGTs in patients with moderate disease activity remains scarce [17]. This subgroup of patients is often underrepresented in clinical trials but represents a significant proportion of real-world RA cases.

This trial aims to address these critical gaps by evaluating the 12-week efficacy and safety of TGTs combined with methotrexate, leflunomide, or hydroxychloroquine in a well-diagnosed population with RA. By focusing on short-term outcomes, the study seeks to identify the most effective and safest TGTs-based regimen, providing evidence to guide clinical practice and improve treatment outcomes for patients with RA globally.

## Methods

### Study Design

This is a prospective, multicenter, open-label randomized controlled trial (RCT) designed to evaluate and generate evidence on the optimal combination of TGTs with other csDMARDs (methotrexate, leflunomide, and hydroxychloroquine). The trial is being conducted at 3 sites in China: Dongzhimen Hospital, Beijing University of Chinese Medicine; Acupuncture and Moxibustion Hospital, China Academy of Chinese Medical Sciences; and Wuhan Hospital of Traditional Chinese Medicine. Eligible patients with RA were enrolled and assigned via block randomization using SAS (version 9.3; SAS Institute). Participants were allocated in a 1:1:1:1 ratio to 1 of 4 treatment groups: group 1 (TGT monotherapy), group 2 (TGTs+methotrexate), group 3 (TGTs+hydroxychloroquine), and group 4 (TGTs+leflunomide). The total observation period was 12 weeks, including a 4-week treatment period, an 8-week treatment period, and a 12-week treatment period. The flowchart of this study is shown in Figure 1, and the evaluation time points are shown in Textbox 1.

**Figure 1. F1:**
[figure not shown]
Flowchart of the randomized controlled trial. RA: rheumatoid arthritis; TGT: Tripterygium glycoside tablet.

Textbox 1.Eligibility criteria for the study.
**Inclusion criteria**
Aged 18-65 yearsDisease Activity Score-28: >3.2 and ≤5.1Men or women without reproductive requirementsNo participation in any clinical trial within 4 weeks before enrollmentProvision of written informed consent
**Exclusion criteria**
Presence of serious organ disease or mental diseaseInability to adhere to medication for 12 weeks due to any reasonDiagnosis of Sjögren syndrome, ankylosing spondylitis, systemic lupus erythematosus, dermatomyositis, or other rheumatic diseasesRenal and hepatic insufficiencyPregnancy or lactation (breastfeeding)Severe gastrointestinal ulcer or active gastrointestinal bleedingUse of glucocorticoids or biological agents within 4 weeks before enrollment

### Setting and Participants

Patients who met the 1987 American College of Rheumatology (ACR) [20] or the 2010 ACR/European League Against Rheumatism [21] classification criteria for RA were eligible for inclusion. The detailed inclusion and exclusion criteria are provided in Textbox 1.

### Recruitment Process

Participants were recruited primarily from the Department of Rheumatology at Dongzhimen Hospital of Beijing University of Chinese Medicine, the Department of Rheumatology at Acupuncture and Moxibustion Hospital at China Academy of Chinese Medical Sciences, and the Department of Rheumatology at Wuhan Hospital of Traditional Chinese Medicine, where research assistants assisted in screening participants. Additional participants were recruited through advertisements such as job postings.

